### Plans to promote participant retention and complete follow-up {18b}

All patients will be counselled before enrolment about the requirements during the trial, in particular about the frequency of follow-up visits. The importance of completing the follow-up will be highlighted, but patients will also be reassured that they can drop out of the study at any time without providing a reason. In addition, participants will be compensated for wage loss and their travel costs.

### Data management {19}

ICMR–National Institute of Malaria research will be responsible for data collection, storage, protection, retention and destruction. All documents will be stored securely and be accessible to trial staff and authorised personnel only. All study data will be recorded on standard Case Report Forms (CRF) and entered into a REDCap database, a GCP-compliant data management system. The database is password-protected and includes internal quality checks to identify data that appear inconsistent, incomplete, or inaccurate. Study participants will be identified by a unique participant number in the database. The study data management plan outlines all activities that will be carried out to ensure security and quality of the data. Subject records at the site will, taking into account the ability of the sites, be stored in binders or scanned and stored electronically. All records will be retained for 5 years following completion of the trial.

### Confidentiality {27}

Study participants will be identified by a unique participant number in the CRF and the electronic database. The trial staff will ensure that the participants’ anonymity is maintained. All documents and data will be stored securely and be accessible to trial staff and authorised personnel only. Only deidentified and anonymised specimens and data will be shared with other research groups.

### Plans for collection, laboratory evaluation and storage of biological specimens for genetic or molecular analysis in this trial/future use {33}

The distinction between relapse and reinfection is an important parameter to understand the epidemiology of *P*. *vivax* malaria and the assessment of treatment efficacy. The cases of recurrence will be classified as relapse or reinfection based on the two genotyping methods PCR and sequencing. The method of PCR-RFLP will be done using *P*. *vivax*-specific highly polymorphic microsatellite markers and genes such as *Pv*MSP3α, *Pv*MSP4, *Pv*MS16, and *Pv*3.27 dried blood spot (DBS) will be made of all the enrolled patients. Parasite DNA will be extracted from DBS for PCR/Genotyping analysis. PCR/genotyping will be undertaken for speciation and genotyping before study drug treatment and in case of days of recurrence.

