#### Interventions

This trial consists of two arms:Intervention arm: 0.50 mg/kg/day primaquine for 7 days (3.5 mg/kg total dose)Control arm: 0.25 mg/kg/day primaquine for 14 days (3.5 mg/kg total dose)

Additionally, all participants in both arms will receive blood schizonticide treatment, i.e. chloroquine (total dose 25 mg base/kg) as per NCVBDC guidelines [6, 7]. All chloroquine doses will be directly supervised.

All patients will be tested initially, and those found to be G6PD deficient (defined as < 30% of AMM) will be excluded from this randomised study but will receive medical care according to WHO guidelines: 0.75 mg/kg/week for 8 doses (total dose 6 mg/kg).

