#### Study procedures for the main study

The screening process will be divided over the period of 2 days (Day − 1 and Day 0), and so will be the process of informed consent. This will be done to accommodate for potential delays in receiving the screening results for the G6PD testing. On Day − 1, a brief informed consent will be taken for initial screening tests and if the participant qualified for enrolment, written informed consent will be taken for enrolment into trial purposes. Detailed procedures are listed in Table 1.

Day − 1: All patients coming to the hospital with fever will be screened. For screening purposes, a brief informed consent will be taken and a venous blood sample will be collected. This will be used for malaria RDT, blood film microscopy, quantification of parasite density, dengue NS1 screening and G6PD testing. Women between the ages of 16 to 49 years willing to participate will be asked to take a urinary pregnancy test. A clinical checklist will be used to evaluate the exclusion criteria. Patients who test positive for vivax malaria will receive their first dose of chloroquine.

Day 0: Participants diagnosed with G6PD deficiency will be informed of their status and will be provided with information on the diagnosis and its consequences in everyday life and referred to a regular hospital clinician for treatment. Haemoglobin will be screened using Hemocue™ machine and patients who meet all enrolment criteria and are willing to provide written informed consent will be enrolled into the trial. Following enrolment, a questionnaire will be completed including demographic information, medical history, treatment history, history of recent blood transfusions, and a thorough physical examination will be performed. A venous blood sample will be taken for CBC and LFT. Dried blood spot (DBS) will be made and will be used for subsequent parasite analyses. All participants will receive the second dose of chloroquine under supervision. Patients in both the arms will receive their first dose of primaquine.

Day 1: All participants will be reviewed and the final dose of chloroquine treatment will be provided. Patients in both study arms will receive their second dose of primaquine. Finger prick blood sample will be collected for haemoglobin measurement and microscopy. Physical examination of urine will be conducted.

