#### Sample collection

Three to 5 ml of EDTA-anticoagulated venous blood sample will be collected on screening (Day − 1) for malaria RDT & microscopy, G6PD testing (UV and Biosensor), dengue NS1 RDT and on enrolment (Day 0) for CBC including Hb estimation, and liver function tests. A venous blood sample will be collected on day of recurrence for CBC and LFT.

Finger prick blood sample will be collected for microscopy and haemoglobin estimation on enrolment and on each subsequent follow-up visit including the first day of each subsequent recurrence.

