#### Dengue NS1 antigen test

The patients will be screened for dengue co-infection at the time of enrolment and during the next 14 days if patients turned febrile again.

For protocol-mandated blood tests that cannot be done immediately, DBS will be made on Day 0 and Day of recurrence for PCR/ genotyping. Any additional tests not listed in the protocol will need ethical approval.

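### The only baseline dried blood spot follows the first chloroquine dose, so the reference genotype for relapse or reinfection calls is pre-primaquine but post-chloroquine

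*Protocol article*

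**What the plan says.** Section {33} of the protocol article plans to classify recurrences as relapse or reinfection by genotype, using DNA extracted from DBS. On timing it says: "PCR/genotyping will be undertaken for speciation and genotyping before study drug treatment and in case of days of recurrence".

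The schedule is set out elsewhere:

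- **Day −1** (Study procedures for the main study): "Patients who test positive for vivax malaria will receive their first dose of chloroquine". Table 1 agrees, with chloroquine marked at screening, Day 0 and Day 1.
- **Day −1 blood** (Sample collection): "Three to 5 ml of EDTA-anticoagulated venous blood sample will be collected on screening", for the malaria, G6PD and dengue tests.
- **Day 0** (Study procedures): "Dried blood spot (DBS) will be made and will be used for subsequent parasite analyses". The same paragraph then lists "All participants will receive the second dose of chloroquine under supervision" and "Patients in both the arms will receive their first dose of primaquine".
- **DBS restated** (under the Dengue NS1 antigen test heading): "DBS will be made on Day 0 and Day of recurrence for PCR/ genotyping". Table 1 likewise has no DBS at Day −1.

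The Interventions section defines the two arms by their primaquine regimen and then adds: "Additionally, all participants in both arms will receive blood schizonticide treatment, i.e. chloroquine (total dose 25 mg base/kg". The term *study drug* is not defined.

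**The concern.** A baseline genotype is the reference against which a later infection is compared. If a clone present at diagnosis is not detected at baseline, a relapse carrying that clone looks like a new infection. Chloroquine acts on the blood-stage parasites that supply the baseline DNA. A sample taken a day into chloroquine may therefore hold fewer detectable clones than one taken at diagnosis. Any such error runs one way, from relapse to reinfection. Section {33} itself presents the distinction as relevant to judging treatment efficacy.

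The wording of {33} adds to the problem. A reader would take it to mean an untreated baseline sample, and the schedule does not provide one for the drug that matters most to blood-stage DNA. Baseline PCR speciation uses the same sample.

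**Working it through.** **Step 1: timing.** There is no stated figure to reproduce, so the check is a comparison of sections.

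| Event | Day | Where |
|---|---|---|
| Venous EDTA sample for screening tests | −1 | Study procedures; Sample collection |
| First chloroquine dose, once vivax-positive | −1 | Study procedures; Table 1 |
| Only baseline DBS | 0 | Study procedures; Dengue NS1 antigen test; Table 1 |
| Second chloroquine dose | 0, listed after the DBS | Study procedures; Table 1 |
| First primaquine dose | 0, listed after the DBS | Study procedures; Table 1 |

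The baseline DBS thus follows one chloroquine dose by about a day. Going by the order of the Day 0 text, it precedes primaquine. The Day −1 tube must precede chloroquine, because the tests run on it produce the positive result that triggers the dose.

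**Step 2: meaning of the {33} sentence.** If *study drug* means primaquine only, the sentence is true. If it includes the chloroquine given under the protocol, it is false. The article supports both readings. The arms are defined by primaquine with chloroquine as an addition, but Table 1 lists chloroquine under Treatment, and Intervention description {11a} describes treatment as chloroquine plus primaquine.

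**Step 3: where the genotype is used.** The primary outcome and the secondary efficacy outcome (Outcomes {12}) count *P. vivax* malaria without genotype correction. The Kaplan–Meier and Cox analyses ({20a}) use the first recurrent parasitaemia of any genotype. The genotype enters only the classification in {33}.

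**Step 4: possible size (illustrative).** Inputs from Sample size {14}: 400 patients, about 13% recurrence on the control regimen, 30% loss to follow-up. Applying 13% to both arms is an assumption.

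- Patients remaining after loss: 400 × (1 − 0.30) = 280
- Expected recurrences, R: 0.13 × 280 = 36.4, and 0.13 × 400 = 52.0

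Assumed, because the documents give nothing: true relapse share *s* of 50–80%; probability *q* of 0–30% that a true relapse is called reinfection because its matching baseline clone was missed after chloroquine.

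Relapses miscalled = R × s × q. Apparent relapse share = s × (1 − q).

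| q | R = 36.4, s = 0.5 | R = 36.4, s = 0.8 | R = 52, s = 0.5 | R = 52, s = 0.8 |
|---|---|---|---|---|
| 0% | 0 | 0 | 0 | 0 |
| 5% | 0.9 | 1.5 | 1.3 | 2.1 |
| 10% | 1.8 | 2.9 | 2.6 | 4.2 |
| 20% | 3.6 | 5.8 | 5.2 | 8.3 |
| 30% | 5.5 | 8.7 | 7.8 | 12.5 |

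The largest cell is 52 × 0.8 × 0.3 = 12.48, or about 12 patients across both arms. There, a true relapse share of 80% would appear as 0.8 × 0.7 = 56%.

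**The case against.** Much of the case on the other side stands.

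- **No flat contradiction.** A reader might infer that {33} is simply wrong. The documents do not support that: the term is undefined, and the sentence holds on the primaquine-only reading. What remains is that the wording does not disclose that the sample is post-chloroquine.
- **Bias is not shown.** A reader might infer that the calls are biased. The documents give no clone-loss rate, no one-day fall in parasite density and no detection limit. An error needs a baseline clone to drop below detection and the relapse to carry that clone. With q at zero, nothing changes.
- **Recurrences are not errors.** All 36–52 expected recurrences are compared with this baseline, but that is the number exposed, not the number misclassified.
- **The trial's result is not threatened.** A reader might infer a threat to the non-inferiority comparison, since {33} links genotyping to efficacy. No planned efficacy analysis uses the genotype, and neither objective in {7} mentions relapse versus reinfection.
- **Arms are treated alike.** Chloroquine and DBS timing are the same in both arms, so no differential error is expected. Equal loss would still shrink a relapse-only risk difference by the factor (1 − q), but the article plans no such comparison.
- **Speciation is supplementary.** Species is established on Day −1 by RDT and double-read microscopy, before chloroquine.
- **The change is not free.** Day −1 consent covers screening tests only, {33} plans DBS for enrolled patients, and Trial status shows that recruitment started on 11/9/23.

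These points limit the consequence. They do not alter the timing, or the fact that an untreated sample is already drawn and not used for genotyping.

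**Conclusion.** The point holds in a limited form. The reference genotype is pre-primaquine but post-chloroquine, and {33} is accurate only if *study drug* means primaquine alone. This creates a possible, one-directional error from relapse towards reinfection. Its size is unknown: about 0–12 miscalled among 36–52 recurrences across both arms, assuming 13% recurrence in both arms, a 50–80% true relapse share and a 0–30% miss rate. That range runs from negligible to material for the classification. Only that classification and the supplementary PCR speciation are exposed. The point still merits action, because the remedy needs no new blood draw, and an untreated baseline sample cannot be obtained once chloroquine has been given.

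**What to change.** In Study procedures for the main study, section {33}, Sample collection, the DBS sentence under Dengue NS1 antigen test, and Table 1, specify that the baseline DBS is made from the Day −1 EDTA tube drawn before the first chloroquine dose. There are two workable routes:

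1. Keep the residual blood and spot it once full consent is given on Day 0.
2. Spot it on Day −1 under an added line in the screening consent, and destroy the spots of patients who are not enrolled.

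Keep the Day 0 spot as back-up. Reword {33} to state the timing relative to both chloroquine and primaquine.

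For patients already enrolled, state that the baseline genotype is post-chloroquine and treat their relapse/reinfection classification as exploratory. Trial status expects recruitment to finish in March 2024, so this may be the part of the fix that covers most patients.

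Cost: no new draw and no change to treatment, but a small consent and sample-handling amendment in a trial that is already recruiting.

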#### Sample collection

Three to 5 ml of EDTA-anticoagulated venous blood sample will be collected on screening (Day − 1) for malaria RDT & microscopy, G6PD testing (UV and Biosensor), dengue NS1 RDT and on enrolment (Day 0) for CBC including Hb estimation, and liver function tests. A venous blood sample will be collected on day of recurrence for CBC and LFT.

Finger prick blood sample will be collected for microscopy and haemoglobin estimation on enrolment and on each subsequent follow-up visit including the first day of each subsequent recurrence.

#### Microscopic blood examination

Specimens will be labelled anonymously (screening number or study number, day of follow-up, date). A fresh Giemsa stain dilution will be prepared at least once a day and possibly more often, depending on the number of slides to be processed. Giemsa-stained thick and thin blood films will be examined at a magnification of 1000× to identify the parasite species and to determine the parasite density.

Two blood slides per patient will be obtained: Both thick and thin blood smear on the same slide. One slide will then be stained rapidly (10% Giemsa for 10–15 min) for initial screening by confirming the presence or absence using the thin smear, while the second slide will be retained. If the patient is subsequently enrolled, the second slide will be stained more carefully (e.g. 6% Giemsa for 45–60 min), and slower staining will also be used for all slides obtained at follow-up visits. The study number of the patient, the date and the day of follow-up will be recorded either on the frosted edge of the slide or on the glass with a permanent glass pen.

On the slow stained slides, thick blood smear for initial screening will be used to count the numbers of asexual parasites as well as sexual (gametocytes) parasites. Thin smear will be used for species identification and parasite stage determination.

The second thick blood smear will be used to calculate the peripheral parasite density, by counting the number of asexual parasites per 500 white blood cells with a hand tally counter. Parasite density, expressed as the number of asexual parasites per μl of blood, will be calculated by dividing the number of asexual parasites by the number of white blood cells counted and then multiplying by the actual white blood cell density (from the CBC reports on Day 0 for enrolled patients).$$\textrm{Parasite}\ \textrm{density}\ \textrm{per}\ \upmu \textrm{l}=\frac{\textrm{Number}\ \textrm{of}\ \textrm{parasites}\ \textrm{counted}\times \textrm{Actual}\ \textrm{WBC}\ \textrm{density}}{\textrm{Number}\ \textrm{of}\ \textrm{leukocytes}\ \textrm{counted}}$$

The same technique will be used to quantify parasite density on each subsequent blood film. A blood slide will be considered negative when examination of 200 high power fields (HPFs) reveals no asexual parasites.

In addition, 100 fields of the second thick film will be examined to exclude mixed infections; in case of any doubt, the thin film will be examined for confirmation. If examination of the thin film is not conclusive, the patient will be excluded from the analysis after complete treatment and follow-up.

Two qualified microscopists will read all the slides independently, and parasite densities will be calculated by averaging the two counts. Blood smears with discordant results (differences between the two microscopists in species diagnosis, in parasite density of > 50% or in the presence of parasites) will be re-examined by a third, independent microscopist, and parasite density will be calculated by averaging the two closest counts. This will be done on days − 1, 0, 1, 2, 7, 14, 21, and 28 and monthly until month 6 and the day of recurrence.

#### CBC and LFT

CBC and LFT will be measured on day 0 and day of recurrence, and repeated in between if the patient reports symptoms (jaundice, pallor) that warrant further investigation. Liver function parameters including total bilirubin, direct bilirubin, alkaline phosphatase, AST/ALT, total proteins, and albumin will be analysed. The tests and all the procedures will be outsourced as per the study protocol.

#### Heamoglobin

Haemoglobin will be measured using a point of care using a Hemocue™, which will be used according to manufacturer instructions. This will be done on days 0, 1, 2, 7, 14, 21, and 28 and monthly till month 6 and the day of recurrence.

#### G6PD deficiency testing

Prior to the study, the local Adjusted Male Median (AMM) will be calculated. G6PD activity will be measured quantitatively by UV spectrophotometer and SD Biosensor both on the day of enrolment. The results of the optimal G6PD activity by spectrophotometer will guide enrolment.

#### Dengue NS1 antigen test

The patients will be screened for dengue co-infection at the time of enrolment and during the next 14 days if patients turned febrile again.

For protocol-mandated blood tests that cannot be done immediately, DBS will be made on Day 0 and Day of recurrence for PCR/ genotyping. Any additional tests not listed in the protocol will need ethical approval.

#### Urine pregnancy test

Female patients of child-bearing age will be asked to take a urine ß HCG pregnancy test before enrolment in the study, because primaquine is contraindicated during pregnancy. Female participants of child-bearing age, defined as those who menstruate or are aged over 12 years, and who are sexually active should use oral contraceptives or barrier contraceptive devices (if oral contraceptives are contraindicated), or using an intrauterine device (IUD) for the duration of the study. Appropriate contraceptive methods will be suggested by the investigator or study team at the time informed consent will be obtained, with appropriate counselling about the risks of becoming pregnant and exposing the foetus to the study medicines.

## Statistical methods

### Statistical methods for primary and secondary outcomes {20a}

#### Efficacy analyses

The efficacy analyses will be based on the modified intention to treat population. Time to first recurrent vivax parasitaemia will be used to compute the Kaplan-Meier estimates of risk of *P. vivax* recurrence at month 6 for treatment arms and control arms with primaquine for each study site. Also, the comparison of the relative hazards between trial arms (hazard ratio (95% confidence interval)) will be estimated from a Cox regression model for the time to the first recurrent episode.

#### Safety analysis

All safety endpoints will be based on the safety population and presented in tabular and/or graphical format and summarised descriptively.

Clinical laboratory data (clinical chemistry and haematology) will be summarised by the mean, median, standard deviation, minimum and maximum values by treatment group and time point. Laboratory data will also be evaluated by tabulating the number and percentage of subjects in each treatment group with values outside specified threshold values of clinical concern (these may include values outside of the normal range, outer range of clinical concern, and other values of clinical concern).

AE reporting will be performed using the MedDRA (Medical Dictionaries for Regulatory Activities) coding system. Each AE coded using the MedDRA system can be associated with more than one system organ class (SOC). However, for reporting purposes, an AE will be associated with the primary system organ class only. Counting of AEs will be based on the number of subjects — not the number of AEs. For example, if a subject reports the same AE on three occasions within a time interval, that AE will only be counted only once. Subjects reporting more than one AE in a system organ class will only be counted once in that system organ class total. AEs considered by the investigator to have a reasonable possibility of being related to treatment (drug-related AEs) will be summarised by preferred term and SOC. AEs leading to premature withdrawal from treatment and or study will be summarised by preferred term and SOC. AEs that are considered to be gastro-intestinal-related (i.e abdominal pain, heartburn, diarrhoea, constipation, nausea and vomiting) will be summarised. AEs that are considered to be haematologically related (i.e clinically relevant drops in haemoglobin or haematocrit or other complications) will be summarised. Serious adverse events will be summarised by preferred term and SOC. All safety data relating to vital sign variables will be presented as summary statistics (including number, mean, median, interquartile range, standard deviation, minimum and maximum).

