The Indian National Center for Vector Borne Diseases Control (NCVBDC) recommends primaquine for the radical cure of vivax malaria in the country. The guidelines recommend caution in areas with a known high prevalence of G6PD deficiency and patients are advised to stop the drug intake if adverse effects occur [6, 7]. To reduce the risk of drug-induced adverse effects, primaquine is recommended at a total dose of 3.5 mg/kg given over 14 days (0.25 mg/kg per day) [7]. However, this prolonged treatment is associated with poor compliance and therefore low effectiveness [8]. To ensure better adherence to the 14-day primaquine regimen, supervised administration of primaquine can be effective and considered to enhance compliance among patients with vivax malaria in India [9]. However, directly observed treatment will require additional costs. An alternative option to increase adherence is a shorter treatment regimen such as a 7-day primaquine course (0.5 mg/kg day over 7 days) which was recently endorsed by WHO [10].

There is limited evidence for the efficacy and safety of this shorter regimen from India and South Asia in general. Two studies have been conducted, one including a sustained release formulation of primaquine [11], and the other was conducted more than 10 years ago [12]. An individual patient data meta-analysis has demonstrated a lack of available evidence on optimal primaquine dosing in South Asia supporting the need for additional data on 7-day primaquine efficacy and safety in India [13].

Our open-label randomised trial aims to compare the efficacy, tolerability and safety of short-course, low-dose (0.50 mg/kg/day for 7 days) primaquine, with the current standard of care (0.25 mg/kg/day for14 days) to prevent *P. vivax* recurrences in India.

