### Objectives {7}

To assess the 6-month efficacy of a 7-day course of primaquine treatment regimen (0.50 mg/kg/day) in preventing recurrent *P. vivax* parasitaemia in G6PD normal patients over 16 years of age compared to the current 14-day primaquine regimen (0.25 mg/kg/day)To assess the safety and tolerability of a 7-day course of primaquine treatment regimen compared to the current standard primaquine regimen.

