##### Safety

The proportion of patients vomiting their medication within 1 hour of administration.The proportion of adverse events and serious adverse events.The incidence risk of anaemia (Hb < 8 g/dL) and/or the risk for blood transfusion.Risk of > 25% fall in haemoglobin on any day of treatment.The incidence risk of an acute drop in Hb of > 5 g/dL during primaquine treatment.Gastrointestinal (GI) tolerability — incidence of abdominal pain, heartburn, diarrhoea, constipation, nausea and vomiting.

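### Safety and tolerability are to be compared between arms, but the protocol plans only per-arm descriptive summaries, with no between-arm difference or interval

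*Protocol article*

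**What the plan says.** The protocol article states a comparative aim for safety in three places: the title, the Background and rationale ("Our open-label randomised trial aims to compare the efficacy, tolerability and safety of short-course, low-dose (0.50 mg/kg/day for 7 days) primaquine", set against the current standard of care), and the second item under Objectives: "To assess the safety and tolerability of a 7-day course of primaquine treatment regimen compared to the current standard primaquine regimen".

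The Outcomes section then lists specific safety outcomes as proportions or risks: vomiting within an hour of a dose, haemoglobin below 8 g/dL and/or transfusion, a fall in haemoglobin of more than 25%, gastrointestinal tolerability, and "The incidence risk of an acute drop in Hb of > 5 g/dL during primaquine treatment".

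The method is given under Safety analysis: "All safety endpoints will be based on the safety population and presented in tabular and/or graphical format and summarised descriptively". The detail that follows is all per arm. Laboratory data are summarised from mean to "minimum and maximum values by treatment group and time point", and also by "tabulating the number and percentage of subjects in each treatment group with values outside specified threshold values of clinical concern". Adverse events are counted by subject, preferred term and system organ class. No difference, ratio or interval between arms appears.

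Under Efficacy analyses, by contrast, the arms are compared through a hazard ratio with a 95% confidence interval.

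**The concern.** Both arms receive 3.5 mg/kg of primaquine in total, but the 7-day arm receives it at 0.50 rather than 0.25 mg/kg/day, twice the daily dose. The Background names drug-induced haemolysis as the hazard of primaquine and says that evidence on the shorter regimen from India is limited. The Discussion says the results will directly inform treatment policy. How much more haemolysis or intolerance the higher daily dose could cause is therefore a question the trial will be asked to answer.

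Severe haemoglobin outcomes may be uncommon. Two small percentages printed side by side invite the reading that the regimens are equally safe, even where the data are compatible with a relevant excess. An interval shows that directly, and the stated plan does not include one.

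The percentages may also not be like for like. Two of the haemoglobin outcomes are limited to the treatment period, which lasts 7 days in one arm and 14 in the other.

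**Working it through.** **1. Objective against method.**

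| Aim | Stated comparison between arms |
|---|---|
| Efficacy (Efficacy analyses) | Hazard ratio with 95% CI |
| Safety and tolerability (Safety analysis) | None; per-arm numbers, percentages and summary statistics |

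The protocol gives no expected event risk, power or precision for any safety outcome, so there is no safety figure to reproduce. Its 68% power concerns recurrence and has no bearing here.

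**2. What an interval would add.** The input from the protocol is 200 patients per arm (Sample size). The event counts are assumptions, chosen only to show the scale.

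The method is Newcombe's interval from Wilson limits, with z = 1.96. For x events in n and p = x/n, the Wilson limits are

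(l, u) = [p + z²/2n ± z√(p(1-p)/n + z²/4n²)] / (1 + z²/n).

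For d = p1 - p2 (7-day minus 14-day), the limits are

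lower = d - √((p1-l1)² + (u2-p2)²), upper = d + √((u1-p1)² + (p2-l2)²).

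| Assumed events, 7-day v 14-day | 7-day % (Wilson) | 14-day % (Wilson) | Difference, points (95% CI) |
|---|---|---|---|
| 6 v 2 | 3.0 (1.38 to 6.39) | 1.0 (0.275 to 3.57) | +2.0 (-1.0 to +5.5) |
| 10 v 4 | 5.0 (2.74 to 8.96) | 2.0 (0.78 to 5.03) | +3.0 (-0.8 to +7.1) |
| 20 v 10 | 10.0 (6.57 to 14.94) | 5.0 (2.74 to 8.96) | +5.0 (-0.2 to +10.4) |

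For the first row, lower = 2.0 - √(1.62² + 2.57²) = 2.0 - 3.04 = -1.0, and upper = 2.0 + √(3.39² + 0.725²) = 2.0 + 3.47 = +5.5.

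With no events in an arm of 200, the exact two-sided 95% upper limit is 1 - 0.025^(1/200) = 1.8%.

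**3. Whether the per-arm percentages are like for like.** The inputs are Table 1, the study procedures and the Haemoglobin section.

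- Primaquine starts on day 0 in both arms. The last dose falls on day 6 in the 7-day arm and on day 13 in the 14-day arm.
- Haemoglobin is scheduled on days 0, 1, 2, 7, 14, 21 and 28, then monthly.
- Read literally, the scheduled post-baseline readings on treatment days are days 1 and 2 in the 7-day arm, and days 1, 2 and 7 in the 14-day arm.

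The 7-day arm thus has one fewer scheduled chance to meet the two on-treatment haemoglobin outcomes, and its day 7 reading, one day after the last dose, falls outside the window. This could understate haemolysis in the arm with the higher daily dose. Symptom-prompted tests may add readings in either arm but do not remove the imbalance in the schedule.

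**The case against.** The best defence is that descriptive safety reporting is common and reasonable for rare events, that only recurrence was powered, and that side-by-side randomised risks are already a form of comparison. No passage promises a test, margin or effect measure for safety. The article is condensed, and a statistical analysis plan that is not shown may add intervals. Calling a summary descriptive does not forbid them.

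Much of this stands. A reader might infer that the trial will give no estimate of the safety difference, or that it cannot answer its second objective. The documents do not support either reading: numbers and percentages per arm are planned for laboratory thresholds, the outcomes are defined as risks, and a crude difference and its interval can be calculated from counts and denominators. Nor is haemoglobin left unused, since it is summarised by arm and time point and feeds the fall and drop outcomes. The choice of interval method and any covariate adjustment are properly left to an analysis plan.

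It would also be wrong to cut the denominator to 140 per arm by applying the 30% loss to follow-up. That allowance belongs to the sample size for recurrence, and nothing suggests it applies to events within at most 14 days of treatment.

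What remains is that the article is not silent on the method. It fixes one for every safety endpoint, and that method stops short of the comparison named in the title and objective.

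**Conclusion.** The point holds as a mismatch between a comparative objective and a stated analysis with no between-arm contrast or uncertainty. It does not show that the safety data will be uninformative. It is a cheap improvement, not a threat to the trial.

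The size can only be illustrated, because the documents give no safety event risks. Under the assumed counts with 200 per arm, observed excesses of 2 to 3 points come with upper limits of 5.5 to 7.1 points, which bare percentages would not show. That intervals are wide for rare events is true of any plan. The reason to print them is to stop a small difference being read as no difference.

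The unequal on-treatment window needs no assumed event risk. It follows from the protocol's own visit schedule if the outcome wording is read literally.

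**What to change.** Add to Safety analysis:

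- For haemoglobin below 8 g/dL or transfusion, a fall of more than 25%, a drop of more than 5 g/dL, vomiting within one hour, and gastrointestinal tolerability, report the number and percentage per arm and the risk difference (7-day minus 14-day) with a 95% CI. Use Newcombe or Miettinen-Nurminen, with exact limits where an arm has no events.
- Present these as estimation, without significance tests.
- Assess the haemoglobin outcomes over one common period in both arms, fixed in advance and using the haemoglobin visits already scheduled. Align the wording of the two on-treatment outcomes with that period.

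General adverse event tables can remain descriptive. A baseline-adjusted analysis of haemoglobin is optional.

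The cost is a few sentences in the protocol or analysis plan and a few extra table rows, with no new data or visits. Intervals for rare outcomes will be wide and should be shown as such.
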